### Exclusion criteria

Participants with the following conditions are excluded:

(1) Transient ischemic attack, reversible neurological deficit.(2) Diagnosed with depression, cognitive impairment, schizophrenia, bipolar disorder, substance abuse, or other mental disorders before stroke.(3) Those who have been confirmed by examination that the neurological deficit is caused by diseases such as brain tumor, brain trauma, cerebral vascular malformation, and brain parasites.(4) Patients with severe forms of heart disease, liver disease, kidney disease, or tumors.(5) Contraindication to an MRI examination.(6) Participating in any other clinical trials.(7) During pregnancy or lactation.(8) Patients who suffer from bleeding disorders, coagulation dysfunction, and skin infections that are not suitable for acupuncture.

### Randomization

The randomization sequence will be generated by an independent statistician, who will not participate in other procedures of the trial, using the SAS 9.3 statistical analysis system (SAS Institute Inc., Cary, NC, USA). To guarantee allocation concealment, the generated list of random numbers will be placed into sequentially numbered, opaque, sealed envelopes. A special information manager will be designated to keep information secure. Researchers need to contact the designated information manager to get a random number and group information for each participant included in the study.

### Blinding

Following the information from the envelope, each participant will be randomly assigned in a 1:1:1 ratio to active acupuncture group, the sham acupuncture group or the waitlist group. Acupuncturists, who had received the prepared standard operating procedure guidance for 2 weeks, will be appointed to perform the acupuncture treatment for both groups separately. The blinding acupuncture device has obtained the national utility model patent certificate (patent number: ZL 202121352221.7). It is a validated device that consists of one tube, one needle base with multiple angle openings, one open or sealing adhesive base, and a pointy or flat acupuncture needle. Figure 2 details the blinding device. The customized blinding needles are produced by a manufacturer with relevant qualifications (Guangzhou Suixin Medical Equipment Co., Ltd.). Before our research, patients will be informed that they may have either “less painful acupuncture” (sham needles) or “traditional Chinese acupuncture” (real needles). As the sham acupuncture in this study can create similar pain to acupuncture without penetrating the skin, it can serve as an effective blinding tool. To maximize blinding effect, both groups will be given identical blindfolds during the treatment. Even so, it is impractical to blind the acupuncture operators due to the acupuncture procedure. In an attempt to minimize the subjective influence, statisticians and data managers, as independent three-party to the research, will also be blinded to the group information.

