### Active acupuncture group

Jin's three-needle therapy is performed by professional acupuncturists. After the acupoint is positioned precisely and the skin to be punctured is disinfected, the needle will be inserted quickly. The location of acupoints is based on the guidelines issued by the World Health Organization (WHO) (47). The subject is asked to take a supine position and wear an eye patch after fully exposing the site to be punctured. Before the intervention, the acupuncturists assemble the tube into the needle base and put the open adhesive base stacking on the target acupoint after skin disinfection with an iodophor cotton swab. The pointy acupuncture needle is passed through the tube into the skin of the subject. Figure 3 shows the acupuncture points, and Table 2 details the locations. Acupoints will be stimulated manually with the depth of insertion varies from 0.5 to 1.5 cun until operating the sense of “De Qi” (48). The reactions of “De Qi” make patients feel soreness, distension, or heaviness, which are vital for acupuncture to react to different nerve conduction (49, 50). After “De Qi” happens, the needles are kept in the acupoints for 30 min without electricity applied. After the needle is removed, the needle hole will be pressed with a sterile dry cotton swab for a while. It must be ensured that the patient is not allowed to remove the eye patch from the start of the acupuncture to the end of the needle withdrawal procedure.

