### Sham acupuncture group

Before the intervention, the acupuncturists assemble the tube into the needle hub and put the sealing adhesive base stacking on the target acupoint after skin disinfection. However, the flat acupuncture needle is passed through the tube into the adhesive sealing base, and the peak of the flat needle can touch the surface skin of the subject to create similar pain as real acupuncture without penetrating the skin. Therefore, it can serve as an effective blinding tool. In both groups, the number of needles inserted, needle retention time, and treatment frequency are the same.

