### The primary outcome

The primary outcome is the change in the performance of anxiety symptoms, which is estimated by the 14-item Hamilton Anxiety Rating Scale (HAMA-14) and the 7-item Generalized Anxiety Disorder scale (GAD-7).

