#### Hamilton anxiety rating scale

The severity of anxiety is often determined by psychological scales. The Hamilton Anxiety Scale (HAMA) is one of the first rating scales to measure the severity of perceived anxiety symptoms. It is considered one of the most widely used rating scales and has been translated into Cantonese (51). A structured interview guide contains a 14-item Hamilton Anxiety Rating Scale of general anxiety, which is rated on a 5-point scale and ranged from 0 (none) to 4 (very severe) by the interviewer.

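### The patient information sets an expected pain difference between the two needle arms, which contradicts the similar-pain basis for blinding and gives patients a cue to their arm

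*Protocol article*

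**What the plan says.** All references are to the protocol article.

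- **Blinding**, on what patients are told beforehand: "patients will be informed that they may have either “less painful acupuncture” (sham needles) or “traditional Chinese acupuncture” (real needles").
- **Blinding**, the next sentence, on why masking should work: "As the sham acupuncture in this study can create similar pain to acupuncture without penetrating the skin". The sentence goes on to call the sham an effective blinding tool.
- **Sham acupuncture group** repeats the premise: the flat needle touches the skin surface to "create similar pain as real acupuncture without penetrating the skin".
- **Blinding**, on visual cues: "both groups will be given identical blindfolds during the treatment".
- **Active acupuncture group**: needles are stimulated manually until De Qi is obtained. "The reactions of “De Qi” make patients feel soreness, distension, or heaviness". No such sensation is described for the sham.
- **The primary outcome** is change in anxiety on HAMA-14 and GAD-7. HAMA is introduced as a scale to "measure the severity of perceived anxiety symptoms", and its items are "rated on a 5-point scale and ranged from 0 (none) to 4 (very severe) by the interviewer". GAD-7 is called a questionnaire; who completes it is not stated.
- **Outcome measures**: all evaluations are made by researchers blinded to allocation.

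**The concern.** The two statements on pain stand next to each other and pull in opposite directions. If the sham hurts about as much as real needling, the less-painful label misdescribes it. If the label is accurate, the stated reason why the sham can mask the arm fails. Either way, patients are told before treatment that pain is what distinguishes the two options.

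This matters because the Abstract gives the lack of a sham control, and hence a placebo effect that cannot be ruled out, as the reason for the trial. The acupuncturists cannot be blinded, so the JTNT-sham comparison leans heavily on the patient not knowing which needle was used. Both primary scales depend on what the patient says about symptoms: GAD-7 through its questions, HAMA-14 through the interview. If patients work out their label and answer accordingly, part of any JTNT-sham difference could be expectation, which is the explanation the sham arm is there to exclude.

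**Working it through.** **Step 1. The statements side by side.**

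| Source | What it implies about pain |
|---|---|
| Blinding, patient information | The two needle types differ: one is less painful |
| Blinding, next sentence | The sham produces similar pain |
| Sham acupuncture group | Similar pain, without skin penetration |

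The first row cannot serve the purpose of the other two.

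**Step 2. Can the cue be used?** Each needle-arm patient has 5 sessions a week for 4 weeks, so 5 × 4 = 20 occasions to compare the sensation with two named options. Blindfolds act on sight only. The patient need not be told that one option is inert: settling on either label identifies the arm.

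**Step 3. The plan's own figures (Sample size).** Inputs: HAMA 14.25 ± 7.10 (JTNT) and 19.46 ± 4.80 (sham), two-sided alpha 0.05, power 0.90, loss 20%.

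- Difference: 19.46 − 14.25 = 5.21.
- Common SD: √((7.10² + 4.80²)/2) = 6.06.
- Normal approximation, n = 2(1.96 + 1.28)² × 6.06² / 5.21²: 29 per group. The unequal-variance t-test gives power 0.894 at 29 and 0.904 at 30, so 30 per group.
- Loss to follow-up: 30/0.80 = 37.5, so 38. Total: 3 × 38 = 114.

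The stated 30, 38 and 114 are reproduced.

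**Step 4. What an expectation shift would do.** The document gives no figure for bias, so the shift b is an assumption and is shown over a range. With no true JTNT-sham difference, 30 per arm and SD 6.06:

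- SE = 6.06 × √(2/30) = 1.56.
- Probability of a significant result = Φ(b/SE − 1.96) + Φ(−b/SE − 1.96).

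| Assumed shift b (HAMA points) | Share of planned 5.21 | Rejection rate at nominal 5% |
|---|---|---|
| 0.5 | 10% | 0.06 |
| 1 | 19% | 0.10 |
| 2 | 38% | 0.25 |
| 3 | 58% | 0.48 |

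With all 38 per arm analysed, SE = 6.06 × √(2/38) = 1.39, and a shift of 1 point gives about 0.11. A larger sample makes a fixed bias more likely to reach significance, not less.

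**The case against.** Several points on the other side have force.

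- **HAMA-14 is not patient-reported.** A reader might infer that both primary outcomes are. The document says that an interviewer rates HAMA-14 and that evaluators are blinded, and it does not say that GAD-7 is self-completed. This stands. Blinded raters protect against rater bias but not against expectation shaping the answers they rate, so the route to HAMA-14 is indirect.
- **Patients may not be told which option is sham.** The words for sham and real needles stand in brackets outside the quoted labels and may be the authors' gloss. The text does not show that patients learn that one option is inert. The point does not need this.
- **Similar is not identical.** A slightly less painful sham could still be called similar, and masking also relies on a device described as validated, on blindfolds, and on equal needle number, retention time and frequency. That softens the conflict but does not remove it: the label still directs attention to pain, and validation is claimed for the device, not for these labels.
- **Parallel design.** Within the trial each patient feels only one needle type. Decoding is therefore possible, not shown.
- **De Qi would differ between the arms under any wording.** This is correct. Neutral labels remove the cue given by the information, not the sensation.
- **Unmentioned waitlist and blinding check.** A reader might infer that patients are not told of the waitlist arm, or that no check of blinding is planned. A condensed article cannot support either inference; both may be covered in the full protocol or the consent form.

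**Conclusion.** The concern holds in a limited form. The document fixes patient wording that sets an expected pain difference between the needle arms, and this contradicts the similar-pain basis for blinding given in the next sentence and in the section on the sham group. The result is an avoidable cue that could bias GAD-7 directly and HAMA-14 through the interview. It concerns the JTNT-sham comparison only, since waitlist patients know that they receive no acupuncture.

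Neither actual unblinding nor the size or direction of any bias can be established from the document. The rates of about 10%, 25% and 48% rest wholly on assumed shifts of 1, 2 and 3 HAMA points in favour of JTNT, the pilot SDs and 30 analysed per arm. They show how sensitive the comparison is and do not estimate this trial's error rate. The sample size itself is reproduced and is not in question.

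**What to change.** 1. Replace the two labels with neutral wording that ties neither pain nor tradition to a needle type, for example two acupuncture devices whose sensation varies from person to person.
2. Reconcile the similar-pain statements in Blinding and Sham acupuncture group with that wording.
3. Record which version of the information each patient received.
4. As a low-cost addition, if not already planned, ask needle-arm patients at the existing week-4 visit, after the scales are completed, which type they think they received. Report the answers by arm beside the JTNT-sham result. This detects decoding; it does not remove cues from De Qi.

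**Cost.** An ethics amendment and one extra question. Recruitment was due to start in May 2022, so patients already enrolled will have had the present labels and the arms may contain two wording cohorts; hence the version record. The question may itself prompt patients to think about their arm before the later follow-up visits, which is a reason to ask it at the end of treatment and not during it.

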**Figure 2 F2:**
[figure not shown]
Schematic diagram of the new acupuncture equipment.

### Interventions and comparison

All groups of patients with PSA will receive routine drugs and rehabilitation treatment during the whole 4-week study, implemented by clinicians and rehabilitation therapists with more than 5 years of clinical experience. All the researchers in this study had received the prepared standard operating procedure (SOP) guidance for 2weeks before the trial. According to the Guidelines for the Prevention and Treatment of Cerebrovascular Diseases in China (46), basic therapeutic drugs with nutritional support, neuroprotection, and secondary prevention drugs will be provided. Additionally, rehabilitation exercises targeting different functions of the subject will be implemented. However, Chinese herbal medicine will be prohibited during the trial. The active and sham acupuncture groups will receive acupuncture treatment five times per week for 4 weeks. The waitlist group will not receive any acupuncture treatment. The specific operations are as follows:

### Active acupuncture group

Jin's three-needle therapy is performed by professional acupuncturists. After the acupoint is positioned precisely and the skin to be punctured is disinfected, the needle will be inserted quickly. The location of acupoints is based on the guidelines issued by the World Health Organization (WHO) (47). The subject is asked to take a supine position and wear an eye patch after fully exposing the site to be punctured. Before the intervention, the acupuncturists assemble the tube into the needle base and put the open adhesive base stacking on the target acupoint after skin disinfection with an iodophor cotton swab. The pointy acupuncture needle is passed through the tube into the skin of the subject. Figure 3 shows the acupuncture points, and Table 2 details the locations. Acupoints will be stimulated manually with the depth of insertion varies from 0.5 to 1.5 cun until operating the sense of “De Qi” (48). The reactions of “De Qi” make patients feel soreness, distension, or heaviness, which are vital for acupuncture to react to different nerve conduction (49, 50). After “De Qi” happens, the needles are kept in the acupoints for 30 min without electricity applied. After the needle is removed, the needle hole will be pressed with a sterile dry cotton swab for a while. It must be ensured that the patient is not allowed to remove the eye patch from the start of the acupuncture to the end of the needle withdrawal procedure.

**Figure 3 F3:**
[figure not shown]
Location range of acupuncture points.

**Table 2 T2:** Specific acupoint location and angle requirements.

**Acupoints**	**Location**	**Insert angle**	**Insert depth**
BaiHui (GV20)	on the head, 5 cun directly above the midpoint of the anterior hairline, or at the midpoint of the line connecting the apexes of the two auricles.		
SiShenZhen	On the head, a total of 4 acupoints are distributed in the front, back, left and right sides of the Baihui acupoint, with 1.5 cun each above BaiHui.	15°	0.5 cun
ShenTing (GV24)	on the head, 0.5 cun directly above the midpoint of the anterior hairline.	15°	0.5 cun
YinTang (GV29)	On the forehead, at the midpoint between the two medial ends of the eyebrow.	15°	0.5 cun
ShenMen (HT7) (bilateral)	On the wrist, in the ulnar depression of the transverse wrist crease, the radial border of the flexor carpi ulnaris tendon.	90°	0.5 cun
SanYinJiao (SP6) (bilateral)	On the inner side of the calf, 3 cun above the tip of the medial malleolus, along the medial border of the tibia.	90°	1.5 cun
HeGu (LI4) (bilateral)	On the dorsum of the hand, approximately on the radial side of the second metacarpal bone, between the first and second metacarpal bones of the hand.	90°	0.5 cun
TaiChong (LR3) (bilateral)	On the dorsal side of the foot, in the subdigital depression to the first metatarsal space.	90°	0.5 cun

1 cun is equal to the width of the interphalangeal joint on the middle finger.

### Sham acupuncture group

Before the intervention, the acupuncturists assemble the tube into the needle hub and put the sealing adhesive base stacking on the target acupoint after skin disinfection. However, the flat acupuncture needle is passed through the tube into the adhesive sealing base, and the peak of the flat needle can touch the surface skin of the subject to create similar pain as real acupuncture without penetrating the skin. Therefore, it can serve as an effective blinding tool. In both groups, the number of needles inserted, needle retention time, and treatment frequency are the same.

### Waitlist control group

During the first 4 weeks, participants in the waitlist group will not receive any acupuncture intervention but will be given compensatory needle therapy after follow-up phase finished.

### Sample size

The sample size was calculated by the primary outcome. According to the results of preliminary pre-experiment, the Mean ± SD of HAMA score in patients who received conventional therapy plus JTNT was 14.25 ± 7.10, while it was 19.46 ± 4.80 in patients who received conventional therapy plus sham acupuncture. Statistical power is set at 0.90, alpha is set at 0.05, and two-sided tests are performed. After calculations performed by PASS 15.0 (NCSS LLC. Kaysville, Utah, USA) software, 30 people are estimated for each group. The estimated loss to follow-up rate is 20%, so each group will eventually need to include 38 people. The formula for sample size calculation is as follow. Therefore, to verify the placebo effect of sham acupuncture, a waiting group was recruited. The number of participants in the waitlist control group is equal as the sham acupuncture group. Finally, a total of 114 participants will be randomly divided into three groups in the proportion of 1:1:1.

(1)
$$\begin{array}{l} N=\frac{{\left(Z_{\alpha }+Z_{\beta }\right)}^{2}*2\sigma^{2}}{\delta^{2}} \end{array}$$

### Outcome measures

Outcomes cover three types of indicators, including scale indicators, serum indicators, and imaging indicators. The assessment of the scale is carried out at baseline, 2nd, 4th, 8, 12, and 16 weeks. CORT and ACTH will be quantitatively detected by ELISA at baseline and 4 weeks of treatment. In addition, ReHo will be used to record the activity of the brain at the baseline and 4 weeks after intervention. All evaluations are conducted by researchers who are blinded to the treatment allocation.

### The primary outcome

The primary outcome is the change in the performance of anxiety symptoms, which is estimated by the 14-item Hamilton Anxiety Rating Scale (HAMA-14) and the 7-item Generalized Anxiety Disorder scale (GAD-7).

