### Study design

A single-center, prospective, randomized controlled trial (RCT) will be conducted at the First Affiliated Hospital of Guangzhou University of TCM. A total of 114 participants with PSA will be recruited and randomly assigned to conventional therapy plus JTNT, conventional therapy plus sham acupuncture, or conventional therapy only. Both JTNT and sham acupuncture are provided five times per week for 4 weeks. Outcomes cover three types of indicators, including scale indicators, serum indicators, and imaging indicators. The primary outcome is the change in the performance of anxiety symptoms, which is estimated by the 14-item Hamilton Anxiety Rating Scale (HAMA-14) and the 7-item Generalized Anxiety Disorder scale (GAD-7). Secondary outcomes are the physical recovery and daily quality of life for patients with PSA, which are evaluated by the National Institute of Health Stroke Scale (NIHSS) and the Modified Barthel Index Scale (MBI). The evaluator will evaluate and analyze the results at six points (baseline, 2nd, 4th, 8, 12, and 16 weeks). ACTH and CORT will be quantitatively detected by ELISA at baseline and 4 weeks of treatment. In addition, ReHo will be used to record the brain regions activity at baseline and 4 weeks after intervention. The flow chart of the trial is illustrated in Figure 1, while Table 1 shows the schedule of measurements.

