### Statistical analysis

#### Clinical data analysis

Third-party statisticians who do not involve in the whole assignment process and implementation of the trial will be invited to conduct statistical analysis. The data will be analyzed using SPSS 26.0 software (SPSS, Inc., Chicago, IL, USA) according to the intention-to-treat principle. The multiple imputation-expectation maximization algorithms are conducted to impute missing data. Continuous variables are summarized as mean ± standard deviation (SD) and tested using a *t*-test or Wilcoxon rank-sum test analysis. Categorical variables are reported in percentage (%) and compared using Pearson's *X*^2^ test or Fisher's exact test. The groups' comparisons are analyzed by *t*-test (independent *t*-test for comparison between the groups; paired *t-*test for comparison within the same group). The non-parametric Wilcoxon rank-sum test or the Mann-Whitney U test will be conducted for the measurement data without a normal distribution or homogeneous variance. All bilateral hypothesis tests with a significance level <0.05 will be considered statistically significant.

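### Two co-primary anxiety scales, no primary visit and no decision rule, with every test judged at 0.05: the stated 0.90 power covers only one HAMA-14 test

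*Protocol article*

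**What the plan says.** The section on the primary outcome, like the Abstract and Study design, gives one construct and two instruments: change in anxiety symptoms "estimated by the 14-item Hamilton Anxiety Rating Scale (HAMA-14) and the 7-item Generalized Anxiety Disorder scale (GAD-7"). It does not say whether one scale or both must show a difference, or at which visit.

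Outcome measures sets the schedule: "The assessment of the scale is carried out at baseline, 2nd, 4th, 8, 12, and 16 weeks". Study design adds "The evaluator will evaluate and analyze the results at six points (baseline, 2nd, 4th, 8, 12, and 16 weeks"). Clinical data analysis specifies an "independent *t*-test for comparison between the groups", with a rank test as the alternative, and closes with "All bilateral hypothesis tests with a significance level <0.05 will be considered statistically significant".

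The Sample size section rests on pilot data for HAMA alone. It states that the "HAMA score in patients who received conventional therapy plus JTNT was 14.25 ± 7.10", against 19.46 ± 4.80 with sham. The design parameters are "Statistical power is set at 0.90, alpha is set at 0.05, and two-sided tests are performed". The visit of the pilot means is not given, and no GAD-7 figure is used.

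**The concern.** A trial whose purpose is to separate JTNT from placebo needs one statement of what counts as success. Here two scales have equal primary standing, results are to be analysed at every visit, and a single sentence grants significance to any test below 0.05. A significant difference on either scale, at any of five visits, could then be reported as success on the primary outcome, and that claim would not carry a 5% error rate. If success instead means both scales, the 0.90 power no longer describes the trial. The text does not say which reading applies, so neither the error rate nor the power of the main conclusion is fixed.

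**Working it through.** **Inputs from the protocol article.** HAMA means 14.25 (JTNT) and 19.46 (sham), SDs 7.10 and 4.80; two-sided alpha 0.05; power 0.90; 30 evaluable per group; 20% loss (Sample size). Two primary scales (The primary outcome). Five post-baseline visits: weeks 2, 4, 8, 12 and 16 (Outcome measures).

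**Inputs assumed.** Correlations of 0.5-0.8 between scales and between visits, with 0.3 between scales also tried. The document gives none.

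**1. The plan's own figure.**
- Difference: 19.46 − 14.25 = 5.21.
- Pooled SD: √((7.10² + 4.80²)/2) = 6.06, so d = 5.21/6.06 = 0.86.
- Normal formula: (1.960 + 1.282)² × 2 × 6.06²/5.21² = 28.4, so 29 per group. The t-test calculation gives 30, with power 0.906.
- Loss: 30/0.80 = 37.5, so 38 per group, and 3 × 38 = 114.

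The figure is correct for one two-sided 0.05 test of HAMA, JTNT versus sham.

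**2. Number of primary tests for that contrast.** Two scales at one visit give 2 tests; two scales at five visits give 2 × 5 = 10.

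**3. Chance of at least one p < 0.05 under the null, JTNT versus sham.** Upper reference if the tests were independent: 1 − 0.95² = 0.098 for 2 tests and 1 − 0.95¹⁰ = 0.401 for 10. Simulated t-tests with 30 per arm give:

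| Family | Any significant result | Significant in favour of JTNT |
|---|---|---|
| 1 test | 5% | 2.5% |
| 2 scales, 1 visit | about 8-10% | about 4-5% |
| 2 scales, 5 visits | about 19-34% | about 10-19% |

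In the second row, correlations of 0.5-0.8 between scales give 8-9%; the 10% end belongs to weaker correlation. In the third row, the low end is correlation 0.8 throughout. The high end is 0.5 with correlation that decays between visits.

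**4. Power under rules that control the error.**
- Both scales must succeed at one visit: type I error stays at or below 0.05. If GAD-7 has the same d = 0.86, joint power at 30 per group is about 0.85-0.87 for a between-scale correlation of 0.5-0.8. If the scales were independent, it would be 0.906 × 0.906 = 0.82.
- Alpha split over two scales (0.05/2 = 0.025 each): power for HAMA at 30 per group is about 0.845. Restoring 0.90 takes 35 per group; 35/0.80 = 43.75, so 44 per group and 132 in total.

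**The case against.** The strongest reply is that this is a condensed article. The primary visit and any hierarchy may stand in a full protocol or analysis plan that is not shown, and the Study design sentence on six points may describe only the assessor's schedule, since it includes baseline. That has force against treating the ten-test family as settled, which is why the one-visit figure is given beside it. It does not remove the point. The article itself makes two scales primary and itself declares every test below 0.05 significant, so a plan that controlled the error would have to overrule this text. Even at one visit the error rate is above 5%.

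It can also be said that the main contrast is clear. That is right. The title, the hypothesis at the end of the Introduction and the Sample size section all point to JTNT versus sham, and the waitlist arm is there to examine the placebo effect of sham.

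Three stronger readings are tempting, and the document does not support them:
- A reader might count all three pairs of arms, 30 tests, and quote an error rate of 40% or more. That treats the waitlist comparisons as confirmatory claims about JTNT, which the text does not.
- A reader might take 19-34% as the chance of falsely declaring JTNT better than sham. Those figures are two-sided, and about half of the false results would favour sham.
- A reader might infer a collapse in joint power, to about 0.60 if GAD-7 had d = 0.6. No GAD-7 effect is given anywhere, so only the direction can be stated: a smaller effect means lower power.

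**Conclusion.** The point holds for the JTNT versus sham comparison. The primary outcome has two scales, no stated visit and no decision rule, under a blanket 0.05 threshold, and the sample size supports one HAMA test only. The false-positive risk in favour of JTNT is roughly double the single-test 2.5% on the narrowest reading, and about four to seven times it (10/2.5 = 4; 19/2.5 = 7.6) if each visit is a chance to succeed. Under the alternative reading, in which both scales must succeed, the error is controlled and power falls modestly below 0.90. The exact percentages rest on assumed correlations, and the joint power on an assumed GAD-7 effect. That the error exceeds 5%, or else that power is below 0.90, does not depend on where in those ranges the truth lies. The sample-size arithmetic itself is sound; its scope is the problem.

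**What to change.** Name one primary hypothesis: HAMA-14 change from baseline, JTNT versus sham, two-sided 0.05, at one stated visit. Week 4, the end of treatment, is the natural choice. The sponsor should confirm that the pilot means come from that visit, and whether they are scores at the visit or changes, because the 0.90 power carries over only if they match the endpoint.

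Then test in fixed order, each step only if the one before succeeds: GAD-7 at the same visit for JTNT versus sham, then HAMA-14 for sham versus waitlist. Report all other visits, scales and pairs with confidence intervals and no confirmatory claim. Replace the closing sentence of Clinical data analysis with this scheme.

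If both scales are to stay primary, state the rule (both must succeed, or Holm) at a named visit, and restate power or sample size for it.

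The first option needs no extra patients or data and leaves 38 per group unchanged. Its price is that GAD-7 becomes a key secondary outcome. Recruitment was planned to start in May 2022, before the article appeared, so the change needs a dated protocol and registry amendment made before unblinding.
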